**Fig. 2 Fig2:**
[figure not shown]
TRACE study schedule of enrolment, interventions, and assessments

### Outcome measures

The primary outcome measure will be the mortality at 30 days after surgery. Secondary outcome measures will be incidence of postoperative complications (in eight domains—infectious, cardiac/transfusion, pulmonary, venous thromboembolic, renal, neurological, surgical, and other—in line with Meguid et al. [14]), time to implement rescue therapy, length of stay in hospital, length of stay in a high-care unit, quality of recovery 30 days after surgery, and postoperative quality of life up to one year following surgery.

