## Background

Perioperative complications occur in approximately 30–40% of non-cardiac surgical patients [1] and are the leading cause of early postoperative morbidity and mortality [2]. Moreover, the occurrence of early complications seems to be associated with long-term mortality that persists for years after surgery [3]. Several studies have demonstrated that surgical complications increase the overall cost of care [4–6]. Therefore, avoiding or even early treatment of complications is valuable in terms of cost-effectiveness [5, 7].

Although there is little variation in the occurrence of complications among hospitals, the resulting in-hospital mortality related to perioperative complications varies considerably [1]. In 1992, Silber et al. created the term failure-to-rescue to describe the percentage of deaths in relation to complications per surgical procedure [8]. Depending on the type of surgery, the failure-to-rescue rate varied widely across hospitals [9, 10]. Most likely, some organizations are able to cover the needs of patients with complications better than others [1, 8, 11, 12]. A more recent trial from the ISOS group observed a failure-to-rescue rate in the range of 1.7–3.6% in a mixed cohort of more than 44,000 patients in 27 countries [13].

Factors contributing to the development of failure-to-rescue have been studied intensely over the past 15 years; however, most of the data come from national or institutional databases and only little is known about failure-to-rescue rates in Europe [13]. It has been hypothesized that regular visits by highly educated and trained health professionals such as intensive care physicians, surgeons, or anesthesiologists can contribute to a decreased incidence of complications by earlier detection and adequate treatment.

Until now, no studies have been performed on the impact of routine postsurgical anesthesia visits on the incidence of postoperative complications. Therefore, we designed a nation-wide study in which patients at risk are routinely followed up by an anesthesia professional at postoperative days 1 and 3, aiming to detect and prevent or treat postoperative complications. Based on the available literature, we hypothesized that routine postsurgical anesthesia visits decrease the incidence of failure-to-rescue and reduce postoperative 30-day mortality by 50%.

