### Research questions

What is the incidence of postoperative complications in this study cohort?Is there an impact of regular anesthesia visits on postoperative days 1 and 3 in reducing postoperative complications, 30-day mortality, and length of stay?What is the impact of the routine anesthesia visits on the time to implementation of rescue therapy, the utilization of high-care and intensive care facilities after complications, and the length of stay in these units?What is the impact of routine anesthesia visits on the quality of recovery 30 days after surgery and on the quality of life one year after surgery?Is the implementation of routine anesthesia visits after surgery cost-effective compared to standard postoperative care?

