### Intervention and control condition

During the intervention phase, all participants will receive a postoperative visit from the anesthesiologist at postoperative days 1 and 3. The postoperative visit is standardized and based on the Modified Early Warning Score (MEWS). The MEWS includes the following measurements: respiratory rate; heart rate and rhythm; systemic oxygen saturation; systolic blood pressure; body temperature; level of consciousness; and urine output. Other measurements include: visual analogue score to assess pain during rest and movement; nausea/vomiting; defecation; and mobilization. In case of a higher MEWS score and/or other concerns, the anesthesia health professional will advise the treating physician on further diagnosis, treatment, and follow-up of the patient.

During the control phase, participants will receive standard care, without a standardized visit from the anesthesiologist. The treating physician may ask the anesthesiologist in consultation when deemed necessary. Standard of care may slightly differ across the different participating hospitals.

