### Data collection

Patient and clinical data will be collected at several time-points during the study period: at inclusion (baseline); intraoperatively; postoperatively at days 1 and 3; during hospital stay; from hospital discharge until 30 days; and until 12 months. Data records will be coded and transcribed by local investigators into an Internet-based electronic case record form.

Data to be collected from patient record files include patient baseline characteristics, data on surgery and anesthesia, intraoperative adverse events, the postoperative clinical course, postoperative in-hospital adverse events, and post-discharge events measured at 30 days and at 12 months after the date of surgery. During the intervention period, data collection additionally includes anesthesia interventions on postoperative days 1 and 3.

Data will also be collected from patient questionnaires, completed at inclusion, seven days, 30 days, and 12 months postoperatively. The questionnaires include questions on quality of life (EuroQol Dutch EQ-5D-5 L), pain scores (numeric rating scale, NRS), functional recovery (Functional Recovery Index), and expected/perceived recovery (Global Surgery Recovery index). See Fig. 2 for an overview of enrolment, intervention, and assessments.

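### The visits search for complications in one phase only, so comparing complication incidence between phases mixes prevention with detection and can attenuate, mask or reverse a real reduction

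*Protocol article*

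**What the plan says.** The Background describes the visits as "aiming to detect and prevent or treat postoperative complications", so detection is part of the intervention's stated purpose. Under Intervention and control condition, each visit follows a standard examination built on an early warning score, with added checks such as pain, nausea and mobilization. If the score is raised or there are other concerns, "the anesthesia health professional will advise the treating physician on further diagnosis, treatment, and follow-up of the patient". In the control phase, "participants will receive standard care, without a standardized visit from the anesthesiologist", although the treating physician may consult the anesthesiologist.

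Under Data collection, the clinical course and adverse events are taken from patient record files and entered by local investigators. It adds: "During the intervention period, data collection additionally includes anesthesia interventions on postoperative days 1 and 3".

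The Research questions ask: "Is there an impact of regular anesthesia visits on postoperative days 1 and 3 in reducing postoperative complications, 30-day mortality, and length of stay". Outcome measures takes up the first part: "Secondary outcome measures will be incidence of postoperative complications", in eight domains, following a cited classification. Statistical analysis compares exposed and unexposed cohorts on binary secondary outcomes by mixed-effects logistic regression with adjustment for time and hospital.

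**The concern.** The exposure can change the probability that the outcome is found and written down. A complication that passes unnoticed under standard care may be noted at a visit, or confirmed by further diagnosis that the visit prompted, and so enter the record from which the outcome is abstracted. Intervention patients could then show more recorded complications even if they had fewer.

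The model cannot separate the two effects. Adjustment for calendar time removes trends shared by hospitals at the same date, and the hospital terms remove stable differences between hospitals. The change in detection is neither: it begins in each hospital at crossover, together with the intervention, so the intervention coefficient absorbs it.

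At stake is the answer to the second research question. A programme that prevents complications could appear ineffective or harmful on this outcome. The budget impact analysis also counts on savings from fewer complications.

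**Working it through.** **The plan's own figure.** The article gives no target effect or power for complications. Its one sample size figure concerns mortality: 2% versus 1%, alpha 0.05 (two-sided assumed), power 80%, 1:1.

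n per arm = [1.960 × √(2 × 0.015 × 0.985) + 0.842 × √(0.02 × 0.98 + 0.01 × 0.99)]² / 0.01² = 2319, so 4638 in total.

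This matches the stated 4638. The present point does not depend on it.

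**Inputs.**
- Complication incidence 30–40% (Background, for non-cardiac surgical patients in general), used here as the true control incidence.
- 2800 patients per phase (Study schedule and randomization).
- Detection probabilities: assumed, because the article gives none.

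**Formula.** Let d be the probability that a complication which occurred is found and recorded. With no false positives, observed incidence = true incidence × d, so

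observed RR = true RR × (d intervention / d control).

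**Break-even.** The observed RR reaches 1 when the detection ratio equals 1 / true RR.
- True 10% reduction: 1 / 0.90 = 1.11.
- True 20% reduction: 1 / 0.80 = 1.25.

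**Range of assumed detection.** The last column is the chance of a significant result in the direction of the observed RR, for true control incidence from 30% to 40% and 2800 per phase, ignoring clustering and time effects.

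| True effect | d control | d intervention | Observed RR | Chance of significance |
|---|---|---|---|---|
| 10% reduction | 0.90 | 0.90 | 0.90 | 64–81% (reduction) |
| 10% reduction | 0.90 | 0.95 | 0.95 | 21–29% (reduction) |
| 10% reduction | 0.90 | 1.00 | 1.00 | no observed difference |
| 10% reduction | 0.80 | 0.90 | 1.01 | about 5% (increase) |
| 10% reduction | 0.80 | 1.00 | 1.125 | 73–89% (increase) |
| 20% reduction | 0.80 | 0.90 | 0.90 | 57–74% (reduction) |
| none | 0.90 | 0.95 | 1.06 | 24–34% (increase) |
| none | 0.80 | 0.90 | 1.125 | 73–89% (increase) |

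Clustering would lower the percentages in the last column but would not remove the bias. The outcome runs from mild attenuation to reversal, depending on inputs that the article does not supply.

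**On the odds ratio scale.** With 35% recorded under standard care, no true effect and 10% more detection, the recorded incidence is 0.35 × 1.10 = 0.385. The odds ratio is (0.385 / 0.615) / (0.35 / 0.65) = 1.16.

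**Failure-to-rescue.** This is deaths in relation to complications. With deaths unchanged and 10% more recorded complications, the ratio is multiplied by 1 / 1.10 = 0.91, a fall of 9%.

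**The case against.** The strongest reply is that nothing in the article shows how large the detection difference is, or that it is large enough to matter. Standard care includes ward surveillance and consultation on request, so control patients are not unobserved. Days 1 and 3 are listed as data collection points without restriction to one phase. Collection continues through the hospital stay and to 30 days, so a complication that would declare itself is found earlier and is not an extra case; inflation would come mainly from mild or self-limiting events. The cited eight-domain classification may carry diagnostic or severity thresholds, and detailed definitions may properly sit in the full protocol or SAP.

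All of this limits the size of the bias. It does not remove the mechanism: equal collection dates do not equalise ascertainment if the record itself differs, and a clear definition of a mild event still needs someone to look for it.

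Two stronger readings are tempting. A reader might infer that better detection will mask or reverse a real reduction. The documents support only that it can, and a true 20% reduction with detection of 0.80 versus 0.90 is attenuated without reversal. A reader might also infer that a planned failure-to-rescue analysis is biased in favour of the intervention. The Background does say "we hypothesized that routine postsurgical anesthesia visits decrease the incidence of failure-to-rescue", but failure-to-rescue is not among the listed outcomes and no analysis of it is described, so only a caution applies.

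It is also fair to object to some obvious replacement endpoints. The research questions ask how the visits change use of high-care and intensive care, so those admissions lie on the intervention's own pathway. Death within 30 days would duplicate the primary outcome.

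**Conclusion.** The point holds as a cheap improvement to a secondary outcome. As planned, the comparison of complication incidence reflects occurrence plus detection, and the expected bias runs against the intervention. The break-even detection ratios of 1.11 and 1.25 follow from the multiplicative formula alone; whether the trial comes near them is unknown. The significance figures rest further on the assumed detection probabilities, a general-population incidence of 30–40%, and no clustering. The result for 30-day mortality is untouched.

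**What to change.** - Keep the eight-domain incidence as a reported outcome.
- Pre-specify beside it, as the comparison that answers the second research question, complications severe enough to be recorded with or without a visit; those leading to reoperation or to readmission within 30 days are examples. Use one definition and only sources present in both phases.
- Report intensive care and high-care admission separately as utilization, since the visits may change it.
- State in advance that the all-complication comparison reflects occurrence plus detection and is expected to be biased against the intervention.
- Where the case record form allows, describe complications first noted at a study visit.
- Attach the same caution to any failure-to-rescue ratio that is reported.

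The cost is a definition in the analysis plan, with fewer events and less precision on this secondary outcome. The article does not say whether the case record form holds severity or the place where a complication was first noted, so that needs checking. Recruitment was still under way when the article was submitted, so the change could precede the analysis.

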### Sample size calculation

The calculation is based on the primary outcome parameter 30-day mortality. In an earlier Dutch study, postoperative all-cause death was 1.85% [15]. Recently, the EUSOS study observed a mortality rate of approximately 2% [16], which is in line with previous results.

We considered a difference of 50% between monitored and non-monitored patients to be clinically relevant. In order to detect a reduction from 2% to 1% in postoperative 30-day mortality, with an alpha of 0.05 and a power of 80%, and a 1:1 ratio between control and intervention group, a total of 4638 patients have to be included in a parallel randomized controlled trial (RCT) design. To compensate for inter-institutional variation, a possible time-effect inherent to the stepped-wedge design, and drop-out, we increased this sample size with 20%. The relatively uncommon approach of applying a 20% inflation factor was discussed extensively during the grant application and ethical approval processes and was finally approved by both the Netherlands Organisation for Health Research and Development and the Medical Ethical Commitee.

Thus, we estimate a requirement of 5600 patients. With eight participating hospitals, this translates into 700 patients per hospital. Figure 1 illustrates how these patients will be divided across hospitals and between the control and intervention groups.

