### Study schedule and randomization

Figure 1 shows the planned study schedule. Total recruitment time covers 31 weeks. All hospitals start in week 1 in the control phase and after week 8 sequentially cross over to the intervention phase. Between the two phases there is a one-week transition period (depicted with an *x*). In week 24, all hospitals will have started the intervention phase.

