### Statistical analysis

Primary and secondary outcome measures (proportions with 95% confidence intervals or means with standard deviations) will be calculated and presented in tables. A patient flow chart will be presented to account for inclusions per hospital and drop-out.

For the primary outcome and binary secondary outcomes, multi-level mixed effect logistic regression with random time by cluster interaction will be used to compare between the cohort that has not and the cohort that has received the intervention according to the stepped-wedge schedule. Time effects will be modelled according to appropriate methods, e.g. using spline functions. For continuous secondary outcomes, multi-level mixed effect linear regression will be used and for countable secondary outcomes, multi-level mixed effect Poisson regression models will be used. Analyses will be performed using SPSS and R.

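### A single 20% inflation of a parallel-trial size cannot cover the time adjustment in this eight-hospital stepped wedge; power for 2% versus 1% mortality is roughly 30–45%, not 80%.

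*Protocol article*

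**What the plan says.** The Sample size calculation section of the protocol article works on 30-day mortality. The target is stated as "In order to detect a reduction from 2% to 1% in postoperative 30-day mortality", "with an alpha of 0.05 and a power of 80" per cent and "a 1:1 ratio between control and intervention group". From this, "a total of 4638 patients have to be included in a parallel randomized controlled trial (RCT) design".

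One factor then takes the plan from that design to the stepped wedge: "To compensate for inter-institutional variation, a possible time-effect inherent to the stepped-wedge design, and drop-out, we increased this sample size with 20" per cent. The result is rounded to 5600, or 700 at each of eight hospitals, and is presented as the number required. The section gives no ICC, no cluster autocorrelation, no stepped-wedge design effect and no drop-out rate. It calls the approach relatively uncommon and notes that the funder and the ethics committee accepted it.

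The schedule is in Study schedule and randomization: 31 weeks, "All hospitals start in week 1 in the control phase and after week 8 sequentially cross over to the intervention phase", with one transition week per hospital and every hospital in the intervention phase by week 24. The text under Fig. 1 gives 2800 patients per condition.

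The Statistical analysis section specifies a mixed logistic model with a random time-by-hospital term. On calendar time it says: "Time effects will be modelled according to appropriate methods, e.g. using spline functions". The same section and the Abstract both repeat that temporal trends are adjusted for.

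**The concern.** In a stepped wedge, early patients are mostly controls and late patients mostly treated. Once calendar time is in the model, the treatment effect is estimated only from the part of treatment status that time does not predict. That loss of information is separate from clustering and usually much larger than a fifth. Here one 20% allowance has to cover this loss, hospital variation and drop-out together.

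The trial hypothesises a 50% reduction in mortality. If power for that effect is well below 80%, a true halving would more often than not give a non-significant result. A reader relying on the stated planning figures could take that result as evidence against the effect.

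**Working it through.** **1. The plan's own figure.** Two-sided alpha 0.05, pooled variance, no continuity correction, p̄ = 0.015:

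n per arm = [1.96·√(2·0.015·0.985) + 0.8416·√(0.02·0.98 + 0.01·0.99)]² / 0.01² = 2318.2, rounded up to 2319, so the total is 4638. This reproduces exactly. Then 4638 × 1.20 = 5566, rounded up to 5600, and 5600/4638 = 1.207. The design can absorb a variance ratio of about 1.2 and no more.

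**2. The schedule.** Fig. 1's grid is not shown, so the steps are inferred. Control runs to week 8, there is one transition week per hospital, and all eight hospitals have crossed by week 24. With equal steps this gives transition weeks 9, 11, …, 23. Each hospital then has 30 recruiting weeks at 700/30 = 23.3 patients. There are 120 control and 120 intervention hospital-weeks, which matches the stated 2800/2800.

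**3. The most favourable case, by hand: no clustering and one linear trend.** The variance ratio is 1/(1 − r²), where r is the correlation of treatment with week over the 240 hospital-weeks.

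- Hospital k (k = 1 to 8) has control weeks 1 to 2k+6. These week numbers sum to 1044 over all hospitals, so the mean control week is 1044/120 = 8.7. By symmetry the mean intervention week is 23.3, and the overall mean is 16.
- Between-condition sum of squares: 240 × 7.3² = 12,789.6.
- Total sum of squares: 8 × 2480 = 19,840, less 168 for the transition weeks, gives 19,672.
- r² = 12,789.6/19,672 = 0.650, so the ratio is 1/0.350 = 2.86.

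The unadjusted standard error is √(4 × 0.015 × 0.985/5600) = 0.00325. With the trend it is 0.00325 × √2.86 = 0.00549. Power = Φ(0.01/0.00549 − 1.96) = Φ(−0.14) = 44%.

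**4. Other cases, by generalised least squares on the same schedule.** The ICC and the autocorrelation (AC) are assumptions, because the article gives neither.

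| Time term | ICC | AC | Variance ratio | Power |
|---|---|---|---|---|
| none | 0 | – | 1.00 | 87% |
| none | 0.01 | 1 | 1.1 | 84% |
| linear | 0 | – | 2.9 | 44% |
| spline or two-week periods | 0 | – | 3.2 | 40% |
| linear | 0.001 | 1 | 3.2 | 41% |
| spline or periods | 0.001 | 1 | 3.6 | 37% |
| linear | 0.01 | 1 | 3.6 | 36–37% |
| spline or periods | 0.01 | 1 | 4.1–4.2 | 33% |
| linear | 0.01 | 0.8 | 4.0 | 34% |
| spline or periods | 0.01 | 0.8 | 4.4–4.6 | 30–31% |

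The first two rows show that 20% does cover clustering when AC is 1. The time adjustment is what breaks the calculation. A 5% drop-out costs a further 1–2 points.

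**5. Simulation.** Binomial data with logistic regression (800 runs per case) rejected in 88% with no time term and no hospital effects. With linear time it rejected in 37–48%, and with period effects in 28–40%. The lower values are those with fixed hospital effects. A logistic mixed model with hospital SD 0.3 on the logit scale and a 3-df spline rejected in 40% (250 runs).

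**6. Detectable effect.** Solve 0.02 − p₂ = (1.96 + 0.84) × √(ratio × 4p̄(1 − p̄)/5600), with p̄ = (0.02 + p₂)/2. A ratio of 2.86 gives p₂ = 0.57% (71% reduction), and a ratio of 4.6 gives about 0.29% (85%). These rates mean about 16 and 8 deaths in 2800, so the normal approximation is rough.

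**The case against.** *The 80% is not claimed for 5600.* This is correct as to wording: it is attached to the parallel trial of 4638. A reader might infer that the article states 80% power for the stepped wedge outright, but no sentence does. The claim is implied, because the inflation is said to compensate for the stepped-wedge time effect and 5600 is then given as the requirement. The fault lies in the factor chosen. The arithmetic is sound.

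*The ICC is not in the documents, and 0.01 is high.* This stands. At 1.5% mortality an ICC of 0.01 means a between-hospital SD of √(0.01 × 0.015 × 0.985) = 1.2 percentage points, close to the mean itself. A logit SD of 0.3 corresponds to about 0.0013, where power is near 37–41%. But at ICC 0 with a straight-line trend the ratio is already 2.9, so the shortfall does not rest on this assumption.

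*The approach was disclosed and approved, and detail may sit in the full protocol or analysis plan.* Disclosure that a method is unusual does not tell a reader that power falls to about half. The factor is stated here, so this is not a matter of missing detail.

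*The all-control weeks 1–8 and the all-intervention weeks at the end.* A reader might infer that these contribute almost nothing once time is modelled. That holds only near ICC 0 with flexible time. When hospitals differ, these weeks help to estimate hospital levels: dropping them raises the ratio from about 4.2 to 5.7 at ICC 0.01 with spline time.

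*A still lower control rate.* A reader might multiply the Background figures for complications and failure-to-rescue (40% × 3.6% = 1.44%) and infer even less power. The documents do not support this. Those figures come from separate, general surgical cohorts, the trial selects high-risk patients, and the sample-size section cites mortality directly (1.85% and about 2%).

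**Conclusion.** The concern holds in this form: the 20% factor does not match the time-adjusted analysis that the article commits to. With 5600 patients, power for 2% versus 1% is roughly 30–45% before drop-out, against the 80% that the planning implies.

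This rests on the inferred two-week steps, even recruitment, a two-sided 0.05 test, a normal approximation, ICC from 0 to 0.01 and autocorrelation from 1 to 0.8. The upper end needs no clustering and a linear trend. The lower end is not a hard floor, since drop-out or fixed hospital effects can take power slightly below it. Power of 80% is reached only for a reduction of approximately 70–85%. That range is approximate, and a narrower one would claim more than a normal approximation supports at so few deaths.

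**What to change.** In the Sample size calculation section, keep 4638 as the parallel-trial reference. Replace the 20% factor with a stepped-wedge calculation on the actual Fig. 1 schedule, by generalised least squares or by simulating the planned mixed logistic model. State the assumed ICC, cluster autocorrelation and drop-out rate.

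Report the result: 5600 patients give roughly 30–45% power for 2% versus 1%, and 80% power is reached only for a much larger reduction (approximately 70–85%, to be confirmed by simulation).

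The cost is one calculation, a rewritten paragraph and a less favourable stated power. Trial status shows recruitment already under way, so this corrects what is disclosed. It asks for no extra patients and no change in conduct.
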